**Supplementary Table 3: Power and Significance Threshold Calculations Summary (minimum sample sizes)**

|                                   | Sponsor Criteria (Non-inferiority) |       |             |       |
|-----------------------------------|------------------------------------|-------|-------------|-------|
|                                   | Sensitivity                        |       | Specificity |       |
|                                   | Power                              | N-I   | Power       | N-I   |
|                                   | 1                                  | 2     | 3           | 4     |
| Test significance level, $\alpha$ | 0.025                              | 0.025 | 0.025       | 0.025 |
| 1 or 2 sided test?                | 1                                  | 1     | 1           | 1     |
| Null hypothesis %, $\pi_0$        | 75%                                | 75%   | 77.5%       | 77.5% |
| Alternative hypothesis %, $\pi_A$ | 83.5%                              | 81.2% | 87.1%       | 84.6% |
| Power (%)                         | 80                                 | NA    | 80          | NA    |
| N                                 | 200                                | 200   | 140         | 140   |

**Supplementary Table 4** summarizes the study design parameters inclusive of:

- the eye-level hypotheses to be tested (non-inferiority)
- the non-inferiority thresholds and offsets
- the sample size requirements, and
- the thresholds needed to establish non-inferiority.

**Supplementary Table 4: Inputs to power calculations for one-sided exact binomial tests**

| Sensitivity                                                                     | Specificity                                                                        |
|----------------------------------------------------------------------------------------|-------------------------------------------------------------------------------------------|
| $H_0: P \leq 0.75$ vs. $H_1: P > 0.75$                                                 | $H_0: P \leq 0.775$ vs. $H_1: P > 0.775$                                                  |
| $p_{baseline} = 0.80$ is the sensitivity target                                        | $p_{baseline} = 0.80$ is the specificity target                                           |
| $p_0 = 0.75$ sensitivity values below 75% are considered inferior to IDx-DR with NW400 | $p_0 = 0.775$ specificity values below 77.5% are considered inferior to IDx-DR with NW400 |
| $p_1 = 0.835$ hypothesized sensitivity of IDx-DR with RV700                            | $p_1 = 0.871$ hypothesized specificity of IDx-DR with RV700                               |

[figure not shown]

| CTMF-SA-DXSDR006-03                                                                                                                                                                   | SAP_2.1_clean                                                                                                                                                                         | Rev. A | Pg. 9 of 16 |
|---------------------------------------------------------------------------------------------------------------------------------------------------------------------------------------|---------------------------------------------------------------------------------------------------------------------------------------------------------------------------------------|--------|-------------|
| $d_0 = -0.05$ non-inferiority difference.
$d_0 = p_0 - p_{baseline}$ and is the maximum distance that may still be considered non-inferior.                                        | $d_0 = -0.025$ non-inferiority difference.
$d_0 = p_0 - p_{baseline}$ and is the maximum distance that may still be considered non-inferior.                                       |        |             |
| $d_1 = 0.085$ is the difference at which power is calculated. $d_1 = p_1 - p_0$ and is the hypothesized sensitivity value above the non-inferiority threshold                         | $d_1 = 0.096$ is the difference at which power is calculated. $d_1 = p_1 - p_0$ and is the hypothesized specificity value above the non-inferiority threshold                         |        |             |
| n=200 mtmDR(+) eyes                                                                                                                                                                   | n=140 mtmDR(-) eyes                                                                                                                                                                   |        |             |
| Reject $H_0$ for at least 163/200 true positive eyes, or at least 81.2% sensitivity.
Establish superiority for at least 172/200 true positive eyes, or at least 85.7% sensitivity. | Reject $H_0$ for at least 119/140 true negative eyes, or at least 84.6% specificity.
Establish superiority for at least 122/140 true-negative eyes, or at least 86.7% specificity. |        |             |

The mtmDR(+) and mtmDR(-) sample size depends on the WRC findings so the study will enroll to a target of 564 eyes (282 subjects maximum) to ensure sufficient numbers for the sensitivity and specificity analyses. In addition, in order to achieve 200 mtmDR(+) eyes, we anticipate >450 mtmDR(-) eyes will be accrued based on the historical enrollment ratio (1:4). Thus, the specificity power will be increased and the threshold to establish non-inferiority and superiority will be reduced. Similarly, in the event that >200 mtmDR(+) eyes are determined, all eyes will be included. Thus, the plan is to include all recruited subjects in the final analyses in support of the intent to diagnose analysis principle.

Additionally, weighted sampling will be performed by sampling with replacement among eyes with ETDRS levels at least 53 for computing sensitivity, PPV, and NPV in settings with higher prevalence of severe disease. The overweight sampling is expected to achieve similar sensitivity due to the samples being drawn at random from the gradable and sufficient eyes with ETDRS greater than 53. This analysis is being done following discussion with FDA to assess PPV and NPV outcomes in populations with different vision threatening incidence.

Simulation studies were performed using the clustered bootstrap approach for confidence interval calculations [12] and similar power levels were achieved to the exact binomial method.

The study will not be powered to test specific subject-level hypotheses; the retrospective power will be computed consistent with the pivotal study performance.

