#### 4. Sample size calculations

**Assumptions:** In this study, a minimum of 200 eyes with mtmDR and at least 140 eyes without mtmDR will be enrolled in the main diagnostic performance study; enrollment will be continued until a minimum of 20 vtDR eyes are confirmed to be sufficient and gradable. The device performance will be evaluated per eye. The primary endpoints will be the sensitivity and specificity of IDx-DR paired with the RV700 in detecting mtmDR based on eye-level results when compared to a PRS by three retinal experts.

[figure not shown]

|                     |               |        |             |
|---------------------|---------------|--------|-------------|
| CTMF-SA-DXSDR006-03 | SAP_2.1_clean | Rev. A | Pg. 8 of 16 |
|---------------------|---------------|--------|-------------|

The predicate device, IDx-DR with the NW400, pivotal trial pre-specified null hypotheses for sensitivity and specificity of 75% and 77.5%, respectively; these represent pre-defined non-inferiority margins. The alternative hypotheses were 85.0% for sensitivity and 82.5% for specificity in support of a non-inferiority design. These lower thresholds for performance will be ruled out with one-sided 97.5% confidence bounds.

As this study is intended to support an extension of the IDx-DR labeling to validate a new camera for use with IDx-DR, the performance is expected to be substantially equivalent to the predicate device at the subject-level.

This study will validate the use of a new camera with the same diagnostic algorithm as currently on the market. The proposed sample size maintains a one-sided 97.5% confidence interval that exceeds the predicate device pivotal trial null hypotheses, i.e., a lower confidence limit  $> 75\%$  for sensitivity and  $> 77.5\%$  for specificity which reflects a 5% non-inferiority offset for sensitivity and a 2.5% non-inferiority offset for specificity (see **Supplementary Table 3** columns 1-4). These hypothesis tests were designed specifically to reflect clinically meaningful eye-level outcomes; substantial equivalence is interpreted as non-inferiority

(**Supplementary Table 3** columns 1-4).

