will involve capturing 4W and OCT retinal images by Fundus Photography Reading Center certified photographers, which together with the RV700 images will be transferred to retinal experts at a qualified reading center to determine the prognostic reference standard (PRS) for each eye, respectively ICDR grading for each eye. The study will reach its primary endpoints if the sensitivity and specificity of IDx-DR paired with the RV700 camera are substantially equivalent to those of the predicate device, IDx-DR.

In order to assure an adequate range of DR conditions in the study population sample, and avoid spectrum bias, for sensitivity and specificity analysis, the primary care study population will be enriched to ensure a sufficient range of diabetic retinopathy severity within cases. The enrichment cohort will be targeted using HbA1c levels.

A total of 36 subjects who participated in the Diagnostic Performance Study will be invited to participate in the Precision Substudy. Of these 36 subjects, 18 will have received a PRS determination of mtmDR(+) for at least one eye, and 18 will have received a PRS determination of mtmDR(-) for both eyes. Each participating subject will undergo a series of nine exams with three different RV700 cameras, three different operators, and three replicates to test the reproducibility and repeatability of using IDx-DR with the RV700.

All clinical study sites will have the adequate subject population and availability of space for at least one operator and one RV700 camera. This space needs to be able to be darkened. Two sites will need space for 3 camera operators and 3 RV700 cameras. Operators cannot have previous fundus imaging experience.

The overall study and the substudy analyses will be performed at both the eye-level and the subject-level for regulatory submission and publication consistent with the de novo study utilizing the Topcon NW400 retinal camera.

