### 9.1.1 Sample Size, Precision, and Power

Minimum sample sizes of  $n=200$  mtmDR+ eyes and 140 mtmDR- eyes will be required. The predicate device, IDx-DR with the NW400, pivotal trial pre-specified null hypotheses for sensitivity and specificity of 75% and 77.5%, respectively; these represent pre-defined non-inferiority margins. The alternative hypotheses were 85.0% for sensitivity and 82.5% for specificity in support of a non-inferiority design. These lower thresholds for performance will be ruled out with one-sided 97.5% confidence bounds.

As this study is intended to support an extension of the IDx-DR labeling to validate a new camera for use with IDx-DR, the performance is expected to be substantially equivalent to the predicate device at the subject-level.

This study will validate the use of a new camera with the same diagnostic algorithm as currently on the market. The proposed sample size maintains a one-sided 97.5% confidence interval that exceeds the predicate device pivotal trial null hypotheses, i.e., a lower confidence limit >75% for sensitivity and >77.5% for specificity which reflects a 5% non-inferiority offset for sensitivity and a 2.5% non-inferiority offset for specificity (**Supplementary Table 8** columns 1-4). These hypothesis tests were designed specifically to reflect clinically meaningful eye-level outcomes; substantial equivalence is interpreted as non-inferiority (**Supplementary Table 8** columns 1-4).

Supplementary Table 8: Power and Significance Threshold Calculations Summary (minimum sample sizes)

---

**Digital Diagnostics Confidential.** This document is intended for internal use only and may not be disclosed or reproduced in whole, or in part, for external distribution in any form without express written permission of DDx Legal. All hard copies should be checked against the current electronic revision prior to use and destroyed promptly thereafter. All hard copies are considered uncontrolled documents.

|                                 | Sponsor Criteria (Non-inferiority) |          |             |          |
|---------------------------------|------------------------------------|----------|-------------|----------|
|                                 | Sensitivity                        |          | Specificity |          |
|                                 | Power                              | N-I      | Power       | N-I      |

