|                                 | 1                           | 2 | 3    | 4 |
| Test significance level, alpha  | 0.025                              | 0.025    | 0.025       | 0.025    |
| 1 or 2 sided test?              | 1                                  | 1        | 1           | 1        |
| Null hypothesis %, $p_0$        | 75%                                | 75%      | 77.5%       | 77.5%    |
| Alternative hypothesis %, $p_A$ | 83.5%                              | 81.2%    | 87.1%       | 84.6%    |
| Power (%)                       | 80                                 | NA       | 80          | NA       |
| N                               | 200                                | 200      | 140         | 140      |

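### The SAP's two superiority rules are not conditional on both co-primary non-inferiority tests, so superiority on one endpoint can be declared in a trial that failed on the other (minor)

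*Combined protocol and SAP*

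**What the plan says.** Sensitivity and specificity are co-primary (protocol 8.1). Protocol 4.1 defines success on both, with the NW400 pairing as comparator: "The study will reach its primary endpoints if the sensitivity and specificity of IDx-DR paired with the RV700 camera are substantially equivalent". Substantial equivalence means non-inferiority, and both documents require a "lower confidence limit >75% for sensitivity and >77.5% for specificity". Of these limits SAP section 4 says: "These lower thresholds for performance will be ruled out with one-sided 97.5% confidence bounds". Supplementary Table 4 turns them into counts: at least 163/200 for sensitivity and at least 119/140 for specificity.

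The same cells then add a second decision for each endpoint. For sensitivity: "Establish superiority for at least 172/200 true positive eyes, or at least 85.7% sensitivity". For specificity: "Establish superiority for at least 122/140 true-negative eyes, or at least 86.7% specificity". The text under the table expects the non-inferiority and superiority thresholds to fall as more negative eyes accrue, and protocol 9.3.1 refers to superiority targets.

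No section writes a superiority hypothesis, gives it an alpha, orders the two superiority tests, or makes them depend on both non-inferiority tests. The table lists 0.80 as the target for each endpoint. Protocol 9.3.1 instead ties the superiority targets to the observed performance of the NW400 in the pivotal trial.

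**The concern.** The non-inferiority tests need no multiplicity adjustment, because both must pass. The superiority rules have no such link. Each is met by a count on one endpoint alone, so the plan as written lets superiority be established on sensitivity while specificity misses its limit, or the reverse.

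For a diagnostic this matters because the endpoints trade off: a system that calls more eyes positive gains sensitivity and loses specificity. A superiority statement on one endpoint is misleading when the other co-primary has failed. There are also two chances of a false claim, with no rule covering the pair. The results are meant for regulatory submission and publication, where such statements would be read.

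**Working it through.** **Inputs.** From SAP Supplementary Table 4: 200 mtmDR(+) and 140 mtmDR(-) eyes; non-inferiority nulls 0.75 and 0.775; targets 0.80 and 0.80; hypothesized values 0.835 and 0.871; the four cut-offs. From Supplementary Table 3: one-sided alpha 0.025, given for the non-inferiority tests. Inferred: 0.80 as the superiority null and 0.025 as its alpha. Assumed: independent eyes and independent endpoints.

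**Reproducing the plan's cut-offs** (exact binomial upper tail, X ~ Bin(n, p)):

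| Rule | Null | P at the cut-off | P one count lower |
|---|---|---|---|
| Sensitivity non-inferiority, 163/200 | 0.75 | 0.0182 | 0.0276 |
| Specificity non-inferiority, 119/140 | 0.775 | 0.0181 | 0.0305 |
| Sensitivity superiority, 172/200 | 0.80 | 0.0179 | 0.0283 |
| Specificity superiority, 122/140 | 0.80 | 0.0185 | 0.0320 |

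Each cut-off is the smallest count with exact one-sided P at or below 0.025. Power for non-inferiority is 80.6% at 0.835 and 80.9% at 0.871, matching the stated 80%. The printed percentages 85.7% and 86.7% lie slightly below 172/200 = 86.0% and 122/140 = 87.1%. This changes no decision at these sizes.

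**A claim in a failed trial.** Because 172 > 163 and 122 > 119, superiority implies non-inferiority on the same endpoint at these counts. The gap arises only through the other endpoint.

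- Sensitivity 0.86, specificity 0.775: P(X ≥ 172) = 0.550 and P(specificity non-inferiority fails) = 1 − 0.0181 = 0.982. Product: 0.540, or 54%.
- Sensitivity 0.80, specificity 0.871: P(X ≥ 122) = 0.556 and P(sensitivity non-inferiority fails) = 1 − 0.335 = 0.665. Product: 0.370, or 37%.

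**At least one false claim, both true values 0.80.** Write a1 = 0.0179 and a2 = 0.0185 for the superiority probabilities, and b1 = 0.335 and b2 = 0.081 for the probabilities of passing non-inferiority.

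- Nominal: 1 − 0.975² = 4.94%. An assumed correlation between the two statistics of −0.5 to +0.5 gives 5.0% to 4.5%.
- Attained, ungated: a1 + a2 − a1·a2 = 3.61%.
- Attained, gated on both non-inferiority tests: a1·b2 + b1·a2 − a1·a2 = 0.73%.
- Difference: 3.61 − 0.73 = 2.88 points. About 80% of the false claims therefore fall in trials where the other co-primary failed.

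**More eyes.** SAP section 4 anticipates more than 450 negative eyes but sets a target of 564 eyes in total, which leaves 564 − 200 = 364.

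| Positive / negative eyes | Ungated | Gated |
|---|---|---|
| 200/140 | 3.6% | 0.7% |
| 200/364 | 3.8% | 1.0% |
| 200/450 | 4.1% | 1.2% |
| 400/1,000 (illustration) | 4.8% | 2.6% |

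The last row shows that gating alone does not hold the pair at 2.5% at every sample size.

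**Comparator.** If the true values equalled the pivotal estimates (87.2% and 90.7%, subject-level), the cut-offs would be met 74% and 94% of the time. Against that benchmark the counts would not test superiority.

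**The case against.** The best defence is that superiority is not a planned hypothesis. Supplementary Table 4 is titled as inputs to power calculations, and its introduction mentions only non-inferiority. The only written hypotheses are against 0.75 and 0.775. No superiority objective or endpoint exists, the analysis sections describe no superiority test, and the protocol's power section has no superiority cut-off. This limits the consequence but does not remove the point: the table still says when superiority is established.

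A reader might infer that the plan states a 2.5% superiority alpha. It does not; that level and the 0.80 comparator are inferred from the cut-offs, and the stated 0.025 belongs to the non-inferiority tests.

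A reader might also infer that false claims run at nearly twice 2.5%. That is the nominal figure with both true values exactly at 0.80. The SAP's own counts attain 3.6%, or 1.4 times 0.025. If only one endpoint is at 0.80, the error stays at or below 2.5%. At the hypothesized 0.835 and 0.871 neither claim against 0.80 would be false. The planned decision is a cluster-bootstrap bound at nominal 97.5%, so 4.9% is still worth quoting, labelled as nominal.

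Finally, the 54% and 37% are not false-positive rates. In those cases the endpoint declared superior really is above 0.80. The claim is true but misleading, because the trial has failed under protocol 4.1.

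**Conclusion.** The point holds and is minor. Followed as written, the two rules allow superiority to be declared on one endpoint after the other co-primary has failed, 54% and 37% of the time in the two cases shown. With both true values at 0.80 and independence, the chance of at least one false claim is 3.6% at 200/140 eyes (nominal 4.9%), against 0.7% with gating. These figures rest on the inferred comparator and alpha and on independent eyes.

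A reader might conclude that the trial's own error rate is inflated. The documents do not support that: success is defined on non-inferiority for both endpoints, so the primary conclusion, its alpha and the sample size are untouched. Only the added superiority statements are affected.

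**What to change.** Choose one of two edits to SAP section 4 and Supplementary Table 4, and carry it into protocol 9.3.1.

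1. Delete the superiority rows, or label them descriptive. This is the simpler choice, since no superiority objective exists.
2. Keep them and add: *Superiority is tested only if both co-primary non-inferiority tests are met, and then in a stated fixed order or by Holm, at one-sided 0.025 overall.* Under Holm, the endpoint with the smaller P value would need 173/200 (exact P 0.0110) or 123/140 (exact P 0.0101). The other would then be tested at 0.025.

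In the same edit, write the superiority null and reconcile its comparator: 0.80 in Supplementary Table 4 against observed pivotal performance in protocol 9.3.1. If the latter is kept, the counts must be recalculated.

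The cost is a sentence or two in each document, with no change to conduct or sample size. Option 2 gives up a single-endpoint superiority claim when the other endpoint fails non-inferiority, and tests the pair of claims slightly more strictly.

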### 7.3. Representation Across Disease Spectrum

To ensure representation across disease spectrum and avoid spectrum bias, a minimum of 200 eyes with mtmDR and 140 eyes without mtmDR will be enrolled at primary care sites for the Diagnostics Performance Study. The study population is expected to mirror the spectrum of disease severity encountered at primary care settings. Of the 200 mtmDR+ eyes, at least 40 eyes are expected to have vtDR.

---

**Digital Diagnostics Confidential.** This document is intended for internal use only and may not be disclosed or reproduced in whole, or in part, for external distribution in any form without express written permission of DDx Legal. All hard copies should be checked against the current electronic revision prior to use and destroyed promptly thereafter. All hard copies are considered uncontrolled documents.

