The study population is expected to mirror the spectrum of disease severity encountered at primary care settings, from no DR to proliferative DR (PDR), with a target sample size of at least 200 eyes (~20% of subject sample size) with more than mild DR (mtmDR+), which includes ETDRS levels 35-85, and/or clinically significant as well as center-involved macular edema as subgroup analyses. The study population is also expected to mirror the racial and ethnic distribution of the US diabetes population. Within this cohort, at least 40 eyes are expected to have vision threatening DR (vtDR), defined as ETDRS level 50-85 and/or clinically significant as well as center-involved macular edema. In addition, the same analyses will be performed at the subject-level for regulatory submission and publication, but the subject-level analyses will not have formal study hypotheses.

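### The enrolment figures in SAP section 4 cannot all hold: 200 mtmDR(+) and more than 450 mtmDR(-) eyes do not fit into 564 eyes (282 subjects)

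*Combined protocol and SAP*

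**What the plan says.** The SAP and the protocol both set a minimum of 200 mtmDR(+) and 140 mtmDR(-) eyes (SAP sections 1, 3.1 and 4; protocol synopsis, 4.1, 7.3, 9.1 and 9.1.1). SAP Supplementary Tables 3 and 4 attach 80% power for sensitivity to the 200 eyes, with null 75%, alternative 83.5%, one-sided alpha 0.025 and rejection at 163 of 200.

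The text after Supplementary Table 4 then gives the enrolment plan: "the study will enroll to a target of 564 eyes (282 subjects maximum) to ensure sufficient numbers for the sensitivity and specificity analyses". It continues: "in order to achieve 200 mtmDR(+) eyes, we anticipate >450 mtmDR(-) eyes will be accrued based on the historical enrollment ratio (1:4".

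Three other statements bear on when enrolment ends:

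- SAP section 4, Assumptions: "enrollment will be continued until a minimum of 20 vtDR eyes are confirmed to be sufficient and gradable".
- Protocol 4.1 says that the population will be enriched by HbA1c. Protocol 7.4 makes enrichment conditional on need, places no limit on the number of enriched participants, and gives no expected mtmDR(+) yield.
- The 564-eye and 282-subject figures appear only in the SAP. The protocol gives minimums and no maximum.

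On vtDR, SAP 3.1 expects at least 20 eyes, defined by ETDRS 53-85 and/or macular edema. Of the 200 mtmDR(+) eyes, protocol 7.3 says "at least 40 eyes are expected to have vtDR", and protocol 4.1 and 9.1 place the ETDRS part of the definition lower ("defined as ETDRS level 50-85").

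**The concern.** The paragraph is meant to show that the enrolment target delivers the eyes the power calculation needs. Read literally, it shows the opposite for sensitivity: the target is smaller than the sum of the two counts it is supposed to produce, and at the paragraph's own ratio the positive eyes fall well short of 200. The negatives would be plentiful, so the whole shortfall lands on sensitivity, one of the two co-primary endpoints. If the figure marked as a maximum were treated as binding, the sensitivity test could be run on little more than half the eyes that its stated power assumes.

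**Working it through.** **Inputs.** From SAP section 4 and Supplementary Tables 3 and 4: p0 = 0.75, p1 = 0.835, one-sided alpha 0.025, exact binomial test, n = 200 mtmDR(+) eyes, 564 eyes, 282 subjects, more than 450 mtmDR(-) eyes, ratio 1:4. The significance level matches the SAP text: "These lower thresholds for performance will be ruled out with one-sided 97.5% confidence bounds".

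**1. Reproduce the plan's power.** Take the smallest r with P(X ≥ r | n, 0.75) ≤ 0.025; power is P(X ≥ r | n, 0.835).

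- n = 200: r = 163, attained alpha 0.0182, power 80.6%. The count and the 80% both match the SAP.
- Specificity as a check on the method (n = 140, p0 = 0.775, p1 = 0.871): r = 119, power 80.9%. This also matches.

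**2. Add up the eyes.**

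- 200 + more than 450 = more than 650 eyes; 650 / 2 = 325 subjects. The stated limits are 564 and 282, so the conflict exists before any ratio is applied.
- At 1:4, 200 positives imply 200 × 4 = 800 negatives: 1,000 eyes, or 500 subjects if both eyes count.
- At 1:4, 564 eyes give 564 / 5 = 112.8 positives and 564 × 4 / 5 = 451.2 negatives.
- For 200 positives within 564 eyes: 200 / 564 = 35.5%, or a ratio of 1:1.82.

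**3. Power at the yield implied by 564 eyes and 1:4.** Same exact test, p1 = 0.835:

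| mtmDR(+) eyes | Reject at | Power |
|---|---|---|
| 112 | 94 | 51.3% |
| 113 | 95 (84.1%) | 49.7% |
| 114 | 95 | 58.0% |
| 141 (1:4 read as one in four: 564 / 4) | 117 | 61.9% |
| 200 | 163 | 80.6% |

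The jump between 113 and 114 comes from the discreteness of the exact test, so roughly 50 to 58% is a fairer description than one value. At n = 113, 80% power would need a true sensitivity of about 86.3%. The same discreteness means that 80% is first reached at n = 183, but that still needs 183 / 564 = 32.4%. With 451 negative eyes, specificity power exceeds 99.9%.

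**4. The subject-based share leads to the same place.** SAP 3.1 and protocol 4.1 and 9.1 give about 20% as a share of subjects, not of eyes. 0.20 × 282 = 56.4 subjects; with two positive eyes each, that is at most 112.8 eyes.

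**5. vtDR.** SAP: at least 20 eyes, lower ETDRS bound 53. Protocol: at least 40 expected, lower bound 50. Both are current texts. Both definitions also admit eyes through macular edema, whereas the weighted analysis resamples eyes at ETDRS 53 or higher. SAP 3.1 ties its 20-eye minimum to that level; the enrolment rule in SAP section 4 counts vtDR eyes. Twenty vtDR eyes therefore need not mean 20 eyes available for resampling.

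**The case against.** The best defence is that 200 positive eyes is a minimum, repeated throughout both documents, and that the 80% is tied to it. Enrollment is monitored by stratum, HbA1c thresholds can be moved monthly, and protocol 7.4 links the final adjustments to the power requirements. A historical 1:4 ratio need not be this study's final mix. All of this stands, and it means that the low power is conditional. It does not settle the paragraph. The SAP labels 282 a maximum, no text says whether the minimum or the maximum prevails, no enrichment yield is stated, and unlimited enriched enrolment sits badly with a fixed ceiling.

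Several stronger readings are tempting but unsupported:

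- *The 80% is wrong, or the trial is planned at 50% power.* The 80% reproduces at n = 200. About 50% arises only if enrolment stops at 282 subjects without enough enrichment.
- *Sites and the CRO hold conflicting stopping instructions.* The maximum is in the SAP alone, so the documents show a conflict within the SAP, not one issued to sites.
- *The plan states a 20% eye-level prevalence.* Its figure of about 20% is subject-based. Only the 1:4 ratio supports an eye-level reading, and its unit is not stated.
- *The 450 was computed from 564 × 0.8.* The match with 451 is suggestive, but the SAP does not say so. Taken alone, 800 negatives also satisfies more than 450.
- *The protocol's 40 vtDR eyes is a stop rule.* It is worded as an expectation.

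**Conclusion.** The enrolment paragraph in SAP section 4 is internally inconsistent, and nothing elsewhere resolves it. The counts exceed the stated ceiling by more than 86 eyes (650 − 564) on the paragraph's own totals, and by 436 eyes (1,000 − 564) if the ratio is applied to 200 positives. Stopping at 282 subjects with a 1:4 mix would leave about 113 mtmDR(+) eyes, 56% of the 200 required, with power of roughly 50 to 58% at 83.5% sensitivity against the stated 80%.

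The power figures treat eyes as independent, as the plan's exact binomial does, and assume that both eyes of every subject are gradable. The primary analysis uses only eyes gradable by both the reference standard and IDx-DR, and no allowance for losses is stated, so both 113 and the 35.5% are on the favourable side. The vtDR mismatch is real but minor and separate.

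**What to change.** Replace the paragraph with one consistent set of figures, in one of two ways:

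1. Delete the word maximum, state that enrolment continues until the 200-eye minimum is met, and restate the expected total in line with the ratio used (1,000 eyes at 1:4, fewer with a stated enrichment yield).
2. Keep 564 eyes and 282 subjects, state that this needs at least 35.5% of gradable eyes to be mtmDR(+), and give the power if the 1:4 mix persists (about 113 eyes, about 50%).

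In either case cite the 1:4 ratio, say whether it counts eyes or subjects, and do not present 20% as a documented eye-level prevalence. Say how the limit, if kept, relates to uncapped enrichment and to the vtDR enrolment rule.

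Separately, reconcile SAP and protocol to one vtDR count and one definition. State the 20-eye enrolment minimum in SAP section 4 for the ETDRS 53-or-higher eyes that the weighted analysis draws from, as SAP 3.1 already does.

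The cost is wording in the SAP and a matching vtDR edit in the protocol. Option 1 may mean more subjects than 282; option 2 means publishing a less favourable conditional power.
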